### Medical history

For all participants document the below information:

- Any history suggestive of CF
  - - Number of chest infections, wet cough, constipation, greasy stools, faltering growth
- Feeding history (breast/bottle/mixed and estimated percentage of each)
- Achievement of age-appropriate developmental milestones
  - Specifically, assessing for achievement of milestones prior to limit ages for areas of gross motor, vision and fine motor, hearing, speech and language, and social behaviour (see details in appendix 2 based on Lissauer, T. and Clayden, G., 2015. *Illustrated textbook of paediatrics*. 4th ed. Edinburgh: Elsevier)(27)
- Medication history
- Has there been continued/new exposure to CFTR modulators:
  - - In-utero (No, Yes (timing and months of exposure))
    - Breast feeding while mother on CFTRm (No, Yes (timing and months of exposure)

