## Endpoints

### Primary endpoints

As an observational study, a combination of multiple endpoints will be monitored to identify areas of interest that may warrant and benefit from future investigation in larger studies.

Below are the endpoints which will be explored based on the currently available literature and research in the field.

*‘Mama’ sub-study*

1. Change in percent predicted FEV_1_ (ppFEV_1_) from pre-conception/baseline to end of pregnancy, and at 12- and 24-months post-partum.
2. Incidence of CF-related pulmonary complications during pregnancy.
3. Incidence of premature delivery (defined as birth <37 weeks gestation).

*Combined ‘Mini’ and ‘Midi’ sub-study*

1. The number of participants with:
2. Liver dysfunction (ALT/AST/GGT/bilirubin above upper limit of normal). This is prospectively obtained in the ‘Mini’ sub-study, and retrospectively reviewed from medical records in the ‘Midi’ sub-study.
3. Presence of congenital abnormalities including cataracts (based on medical history and examination)
4. The number of participants with normal IRT subsequently diagnosed with CF (based on a combination of CF genetic tests, sweat chloride, and faecal elastase where appropriate)
5. The number of participants with an abnormal lung clearance index (LCI) (‘Midi’ only)

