### Exploratory endpoints

*‘Mama’ sub-study*

Quantitative endpoints are:

1. Obstetric-specific:
   1. Caesarean section rate
   2. Incidence of medically initiated delivery for pulmonary indication
   3. Incidence of intrahepatic cholestasis
   4. Incidence of pregnancy induced hypertension.
   5. Incidence of pre-eclampsia
   6. Incidence of gestational diabetes
   7. Incidence of large or small for gestational age infants
   8. Incidence of postnatal anxiety/depression (as noted by EPNDS or patient-reported following clinical assessment by other healthcare providers)
   9. Obstetric outcomes according to chronic airways pathogen colonisation history
   10. Obstetric outcomes according to micro-nutritional or early pregnancy hormonal status.
   11. Obstetric outcomes according to diabetes status and therapy (CF diabetes, gestation diabetes, no diabetes)
2. CF-specific:
   1. Incidence of pulmonary exacerbations during pregnancy and within first 24 months requiring oral and/or IV antibiotics.
   2. Variability in lung function during and post-pregnancy as shown by OE-MRI
   3. Sweat chloride levels during pregnancy, and variability per trimester.
   4. Change in weight from pre-conception until pre-delivery.
   5. Change in CFQ-R, EQ-5D-5L, PHQ9 and GAD7 scores.
   6. Bronchial artery size assessment (by MRI) at baseline/pre-conception, antenatal and post-partum (6-12 months).
   7. Change in haemoptysis frequency from baseline, and during pregnancy (as per number episodes per person-years pregnant), and post-partum.
   8. Change in weight according to breast-feeding status in first 24 months post-partum.
   9. Validation of CFTRm assays in serum and breastmilk.

Qualitative endpoints:

1. Thematic analysis of experiences of females with CF throughout:
   1. Family planning,
   2. Pregnancy and childbirth,
   3. Early parenthood.

*Combined ‘Mini’ and ‘Midi’ sub-study*

Exploratory endpoints are:

1. Number of participants with below neonatal birth outcomes:
   1. Prematurity (defined as being born < 37 weeks' gestation)
   2. Low birth weight < 2^nd^ centile
   3. Special care or neonatal intensive care unit admission
2. Frequency of raised blood pressure (>95^th^ centile for age, sex and height on two separate readings)
3. Frequency of faltering growth (definition as per NICE guidelines [NG75])
4. Frequency of delayed development past limit ages in gross motor, vision and fine motor, hearing, speech and language, and social domains. (see appendix 2)

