### Primary endpoint analysis

A descriptive analysis of the endpoints will be completed. For categorical variables (e.g. presence of cataracts) they will be summarised as frequencies (%). For continuous variables (e.g. weight centiles) they will be reported as a mean (standard deviation) or median (inter-quartile ranges) dependent on sample distribution.

For comparisons across CFTRm exposed and non-exposed groups, a chi-square or Fisher’s exact test will be used for categorical variables, and a two-sample t-test or Mann-Whitney U test for continuous variables. Confounders including but not limited to cumulative time of exposure to CFTRm, maternal health, and gestation of offspring will be considered.

In the ‘Mini’ sub-study, enrolling offspring for their first visit up to the age of 12 months allows for maximising sample size although resulting in the possibility of missing early life events. A sensitivity analysis to test assumptions such as only including those up to six months of age will be undertaken.

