### Exploratory endpoint analysis

The same approach will be taken as for the primary endpoint analysis.

The interviews in the ‘Mama’ sub-study will be pseudo-anonymised and recorded and transcribed live within MS Teams. The transcripts will be anonymised and imported into NVivo. The interviews will be analysed in this programme using thematic analysis, in a structure similar to that described by Braun and Clarke in their 2006 seminal paper (1). The proposed primary analyser has experience of thematic analysis and grounding in the subject matter. This will be done in an iterative way with analysis happening alongside ongoing data collection. As is common practice in qualitative interviews, the interview guides may be revised if new themes evolve that require further exploration (2,3). To increase the robustness, theme checking will be performed by members of the study team, and member checking will be performed by participants prior to any publication (2,3).

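### Section 15.4.2 lists the dose of the exposure (cumulative CFTRm time) and an outcome of it (gestation) as confounders of the exposed/non-exposed comparison

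*Protocol*

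**What the plan says.** Section 15.4.2 sets up a two-group contrast: "For comparisons across CFTRm exposed and non-exposed groups, a chi-square or Fisher’s exact test will be used for categorical variables". The other pair of tests named there is "a two-sample t-test or Mann-Whitney U test for continuous variables". The sentence that follows in the protocol is "Confounders including but not limited to cumulative time of exposure to CFTRm, maternal health, and gestation of offspring will be considered". No regression, stratification or matching is named.

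Section 9.4.4 shows how exposure is captured. In utero it is "In-utero (No, Yes (timing and months of exposure"; through lactation it is "Breast feeding while mother on CFTRm (No, Yes (timing and months of exposure".

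Gestation also appears among the endpoints. Section 15.2.1 has a primary Mama endpoint, "Incidence of premature delivery (defined as birth <37 weeks gestation". Section 15.2.2 has an exploratory Mini/Midi endpoint, "Prematurity (defined as being born < 37 weeks". Section 15.4.3 then says of the exploratory endpoints: "The same approach will be taken as for the primary endpoint analysis".

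**The concern.** A confounder is a separate cause of both exposure and outcome. Cumulative time on CFTRm is the exposure on a finer scale. A child recorded as No on both routes has zero months, and any other child has more than zero. Exposed status is therefore fully determined by duration, and no non-exposed child shares a duration with an exposed child.

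Gestation at birth is fixed only after in-utero exposure has begun. Any effect of CFTRm on birth weight, neonatal unit admission or early liver tests that acts through earlier delivery would be blocked by adjusting for it. Where prematurity is the outcome, adjusting for gestation is circular.

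The contrast bears on liver dysfunction and congenital abnormalities including cataracts. If the list were carried into a model, the error would tend towards false reassurance.

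**Working it through.** The protocol gives no significance level, power or powered sample size, so there is no figure to reproduce. The check is algebra plus illustration.

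**Algebra.** Fit outcome = a + b·(exposed) + c·(months), with months equal to 0 for all non-exposed children. The non-exposed fix a at their mean, ȳ0. The exposed determine a + b (their regression line at zero months) and c (its slope). With ȳ1 and d̄ the exposed group's mean outcome and mean months:

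- b = (ȳ1 − ȳ0) − c·d̄
- Var(b) = σ²·[1/n0 + 1/n1 + d̄²/Σ(d − d̄)²], the sum being over exposed children

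So b compares non-exposed children with hypothetical children exposed for zero months. If the effect is proportional to months, ȳ1 − ȳ0 is about c·d̄ and b is about 0. If any exposure has the same effect, c is about 0 and b is unbiased, but the last variance term is added.

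**Inputs.** From section 15.3.2: 25 to 35 Mini infants. Assumed, because the protocol does not give them: 50%, 67% or 80% exposed; outcome SD 1; mean effect 1 SD; two-sided 5% test; in-utero exposure of 9 months for 85% of exposed children and 1 to 8 months (uniform) for 15%; half also exposed by lactation for 1 to 12 months (uniform).

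**By hand, 20 exposed and 10 non-exposed.**

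- Mean months: 0.85×9 + 0.15×4.5 + 0.5×6.5 = 8.325 + 3.25 = 11.575.
- In-utero variance: 0.85×81 + 0.15×(4.5² + 7²/12) − 8.325² = 3.19.
- Lactation variance: 0.5×(6.5² + 11²/12) − 3.25² = 15.60.
- Total variance 18.79, so Σ(d − d̄)² is about 19×18.79 = 357.
- SE without months: √(1/10 + 1/20) = 0.39.
- SE with months: √(0.15 + 11.575²/357) = √(0.15 + 0.375) = 0.72.

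**Simulation, 2,000 runs per scenario.** Nine scenarios: N = 25, 30, 35, each with the three exposed shares.

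| Truth | Coefficient, without → with months | SE | Power |
|---|---|---|---|
| Proportional to months, N = 30, 67% exposed | 1.00 → 0.00 | 0.40 → 0.74 | 67% → 5% |
| Proportional to months, all nine | about 1.00 → about 0.00 | 0.35–0.52 → 0.67–0.94 | 43–80% → 4–6% |
| Fixed effect, N = 30, 67% exposed | 1.00 → 0.99 | 0.39 → 0.74 | 69% → 25% |
| Fixed effect, all nine | about 1.00 → about 1.00 | 0.33–0.49 → 0.67–0.93 | 47–83% → 18–31% |

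Under the fixed effect the SE ratio runs from 0.67/0.42 = 1.6 (N = 35, 80% exposed) to 0.93/0.39 = 2.4 (N = 25, 50% exposed). The correlation of exposed status with months is 0.77 to 0.90.

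**Gestation.** Assume that exposure shortens gestation by 1 week, that the outcome changes by 0.4 SD per week, and that there is no other path. The true total effect is 0.40 SD. With N = 30 and 67% exposed (3,000 runs), the unadjusted estimate is 0.38. Adjusted for gestation it is −0.02.

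**The case against.** The strongest reply is that the criticised model is not in the protocol. The named tests are unadjusted, the variables are only to be considered, section 15.1 describes a descriptive analysis, and a statistical analysis plan will be written before final analysis. That stands, and it limits the severity. It does not make the list right: duration is put forward as a confounder, and a later plan could carry that over.

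Second, the effect disappears only if it scales with duration. That also stands: under an all-or-none effect the estimate is unbiased and the loss is precision. The simulations also use a continuous outcome, whereas the offspring primary endpoints are counts of children with an abnormality.

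Third, gestation can be a reasonable covariate. It precedes lactational exposure, and a declared direct-effect analysis may condition on it. The non-exposed group can include children whose father has CF, and sections 4.1 and 4.2.2 report more preterm birth in CF pregnancies, so gestation may carry differences unrelated to the drug. That is a reason to report it and examine its influence. It does not rescue adjustment when prematurity is the outcome or the total in-utero effect is wanted.

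A reader might go further and infer that the study is committed to adjusting a real effect away, or that maternal health is also a wrong choice. The documents support neither. No adjusted model is specified, and the protocol does not fix when maternal health is measured; measured before exposure, it is a reasonable confounder.

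**Conclusion.** The point holds as a misclassification of two listed variables. Cumulative exposure time is the dose of the exposure, which follows from section 9.4.4 without any assumption. Gestation follows the start of in-utero exposure and is also an endpoint, which follows from sections 15.2.1, 15.2.2 and 15.4.3.

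The numerical consequence is conditional on the list being carried into an adjusted analysis. The contrast then tends to zero if the effect scales with duration; otherwise it stays unbiased with a standard error 1.6 to 2.4 times as large. These sizes rest on the assumed exposed share, effect and duration pattern, not on protocol data.

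Severity: should-fix. The study is exploratory, has no power calculation, and says only that the variables will be considered.

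**What to change.** Rewrite the confounder sentence in section 15.4.2:

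- Remove cumulative exposure time from the list. Analyse months in utero and months via lactation as dose-response variables among exposed children only.
- Do not adjust for gestation when prematurity is the outcome or when estimating the total in-utero effect. Keep it for the lactational comparison, or as a sensitivity analysis labelled as a direct effect.
- Restrict maternal health to characteristics that predate exposure and are already recorded under section 9.4.2, such as maternal age and pre-existing comorbidities. Keep covariates few, given 25 to 35 infants.

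A longer adjustment set is not advised. Section 9.4.2 does not list pre-pregnancy ppFEV1 or BMI, and mothers outside Mama would lack them. Adjusting for which parent has CF would leave the contrast resting on the few non-exposed children of mothers with CF. At the roughly 90% continuation rate in section 4.1, even if all 25 to 35 infants had mothers with CF, that is about 0.10×25 = 2.5 to 0.10×35 = 3.5 children.

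The cost is one rewritten sentence, carried into the statistical analysis plan. No new data are needed.

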### Exploratory endpoint analysis

The same approach will be taken as for the primary endpoint analysis.

The interviews in the ‘Mama’ sub-study will be pseudo-anonymised and recorded and transcribed live within MS Teams. The transcripts will be anonymised and imported into NVivo. The interviews will be analysed in this programme using thematic analysis, in a structure similar to that described by Braun and Clarke in their 2006 seminal paper (1). The proposed primary analyser has experience of thematic analysis and grounding in the subject matter. This will be done in an iterative way with analysis happening alongside ongoing data collection. As is common practice in qualitative interviews, the interview guides may be revised if new themes evolve that require further exploration (2,3). To increase the robustness, theme checking will be performed by members of the study team, and member checking will be performed by participants prior to any publication (2,3).

## Interim analysis

With this an observational exploratory study no formal interim analysis will take place.

## Other statistical considerations

Any change in statistical plan will be discussed with an Imperial University statistician and clearly outlined in the final study report.

# Committees in involved in the study

## Study Management Group

A Study Management Group will be formed for this study, comprising grant holders and lead investigators, clinical members of the study team and a study co-ordinator. The role of the group is to monitor all aspects of the conduct and progress of the study, ensure that the protocol is adhered to and take appropriate action to safeguard participants and the quality of the study itself.

## Independent Advisory Group

Co-applicants on the Matriarch_CF grant include lead investigators and senior clinicians from the Mayflowers(10) study group, who have agreed to provide independent review and advice on the design and analysis of this study.

## Patient and Public involvement

A person with CF was also a co-applicant on the Matriarch_CF grant has reviewed the protocol and study design for acceptability and provided input.

Members of the potential study population have also been consulted as part of the study design and will continue to be involved through its duration.

# Direct access to source data

The Investigator/institution will permit study-related monitoring, audits, REC review, and regulatory inspection(s), providing direct access to source data/documents. Study participants are informed of this during the informed consent discussion. Participants will consent to provide access to their medical notes.

# Ethics and regulatory requirements

The Sponsor will ensure that the study protocol, Patient Information Sheet (PIS), Informed Consent Form (ICF) and submitted supporting documents have been approved by a main Research Ethics Committee (REC), prior to any patient recruitment taking place. The protocol and all agreed substantial protocol amendments will be documented and submitted for ethical and regulatory approval prior to implementation.

Before the site can enrol patients into the study, the Principal Investigator must apply for Site Specific Assessment from the Trust Research & Development (R&D) and be granted written confirmation of C&C. It is the responsibility of the Principal Investigator to ensure that all subsequent amendments gain the necessary approval. This does not affect the individual clinician’s responsibility to take immediate action if thought necessary to protect the health and interest of individual patients.

Within 90 days after the end of the study, the CI and Sponsor will ensure that the main REC and HRA are notified that the study has finished. If the study is terminated prematurely, those reports will be made within 15 days after the end of the trial.

# Monitoring plan for the study

The study will be monitored according to the monitoring plan agreed and written by the Sponsor, based on the internal risk assessment procedure. Where appropriate the CI will be asked to complete a copy of the Sponsor’s self-monitoring template. It is the responsibility of the CI to ensure this is completed and submitted to the RO on request (see Study Monitoring Plan). It is the responsibility of the RO to determine the monitoring risk assessment and explain the rationale.

The CI will be provided with a copy of the study monitoring report during the study initiation monitoring visit.

# Finance

This study has been funded by a Strategic Research Centre grant from the Cystic Fibrosis Trust for three years. Additional funding for a paediatric research fellow is covered by Guy’s and St Thomas’ NHS trust and investigator discretionary funds. Funding for a lung physiologist to carry out LCI is also from investigator discretionary funds. Funding was provided by NIHR for a clinician to carry out the interviews in the ‘Mama’ sub-study.

# Insurance and indemnity

NHS bodies are liable for clinical negligence and other negligent harm to individuals covered by their duty of care. NHS Institutions employing researchers are liable for negligent harm caused by the design of studies they initiate. The provision of such indemnity for negligent harm should be stated to the participant.

# Publication policy

Data ownership rights will lie with the institution. Resultant publications or presentations will adhere to Good Publication Practices and International Committee of Medical Journal Editors (ICMJE) guidelines. Results of this study will be submitted as part of MD and doctoral theses and for publication in peer reviewed journals. The CI in conjunction with the clinical research team will prepare the manuscript(s); authorship will be determined by mutual agreement. The CI must review any secondary publications and presentations prepared by investigators.

# Statement of compliance

The study will be conducted in compliance with the protocol, Sponsor’s Standard Operating Procedures (SOPs), GCP and the applicable regulatory requirement(s).

The study conduct shall comply with all relevant laws if directly applicable or of direct effect and all relevant laws and statutes of the UK country in which the study site is located including but not limited to, the Human Rights Act 1998, the Data Protection Act 1998, the Medicines Act 1968, Good Clinical Practice, and with all relevant guidance relating to medicines and clinical studies from time to time in force including, but not limited to the World Medical Association Declaration of Helsinki entitled 'Ethical Principles for Medical Research Involving Human Subjects' (2008 Version), the UK Policy Framework for Health and Social Care Research (as amended).

This study will be conducted in compliance with the protocol approved by the REC and according to GCP standards. No deviation from the protocol will be implemented without the prior review and approval of the Sponsor and REC except where it may be necessary to eliminate an immediate hazard to a research subject. In such case, the deviation will be reported to the Sponsor and REC as soon as possible.

# List of Protocol appendices

**Appendix 1** *Sample Structured Interview Questions*

**Preconception interview**

- Does having CF influence your decision on whether to have a baby, and if so, in what ways?
- If you have been taking Kaftrio, do you think your experience around this medication and its impact influenced your desire for family planning?
- Do you have a feeling for what you’re planning to do about taking Kaftrio during pregnancy? What’s leading you towards this decision?

**Pregnancy interview**

- How has your experience of pregnancy been so far? Any challenges you’d like to share?
- How do you think your CF has impacted on your pregnancy journey? How has your experience been with fitting in your CF therapies?
- What have you been doing with your Kaftrio during pregnancy, and what led you to do this?
- Has your pregnancy been similar or different to your expectations?
- What are your hopes and plans for your delivery, and do you think your CF has influenced your delivery plans?

**Postpartum and early parenthood interview**

- How was your experience of childbirth? Did you feel that your hopes and concerns with regards the birth plan were jointly taken into consideration with regards your cystic fibrosis?
- And how was/is your mental/emotional health in the weeks after delivery?
- Did you have considerations which are CF-specific around breastfeeding? What did you do about your Kaftrio and what led to this decision?
- How do you think your CF impacts on your experience of being a mother?
- And what about your partner’s experience?
- How do you fit in all your health needs around parenthood? (e.g. appointments, physio, medications such as nebulisers?)

**Appendix 2** Limit ages for developmental milestones adapted from Lissauer T, Clayden G. Illustrated textbook of paediatrics. 4th edition. Edinburgh: Elsevier; 2015.

| **Gross motor skills** | | **Vision and fine motor** | | **Hearing, speech, and language** | | **Social behaviour** | |
| --- | --- | --- | --- | --- | --- | --- | --- |
| **Milestone** | **Limit age** | **Milestone** | **Limit age** | **Milestone** | **Limit age** | **Milestone** | **Limit age** |
| *Head control* | 4 months | *Fixes and follows* | 3 months | *Polysyllabic babble* | 7 months | *Smiles* | 8 weeks |
| *Sits unsupported* | 9 months | *Reaches for objects* | 6 months | *Consonant babble* | 10 months | *Fear of strangers* | 10 months |
| *Stands independently* | 12 months | *Transfers objects* | 9 months | *Saying 6 words with meaning* | 18 months | *Feeds self with spoon* | 18 months |
| *Walks independently* | 18 months | *Pincer grasp* | 12 months | *Joins words* | 2 years | *Symbolic play* | 2 – 2.5 years |
|  |  |  |  | *3-word sentences* | 2.5 years | *Interactive play* | 3 – 3.5 years |

